### Withdrawal and drop-out

2.7.

All participants are free to withdraw from the study at any time and are not required to give any reason for doing so. If a participant at any time does not fulfill the in- and exclusion criteria, they will be withdrawn from the study, except if this is solely the progression from moderate to severe AD. The principal investigator may additionally halt the trial for an individual participant or the entire trial, should there be any major safety concerns with the continuation of the study.

In case of drop-outs or missing data for any other reason, a last observation carried forward approach will be used to handle the missing data.

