### Aim, study design, and setting

2.1.

This study will examine whether the entrainment of 40 Hz neural oscillation by novel 40 Hz Invisible Spectral Flicker is a potential therapy for AD. The study design will be a randomized, double-blinded (investigator, participant), placebo-controlled clinical trial. One arm of the study will receive active treatment with 40 Hz ISF, while the other arm will receive a placebo consisting of an identical sham device with non-flickering white light. The study will be conducted at the Zealand University Hospital, which is host to the regional memory clinic and the main diagnostic institution for neurological disease in the region of Zealand with an approximate population of 842.000 people (Danmarks Statistik, 2021). The intervention will last for 6 months (26 weeks) followed by 6 weeks of no intervention, see Figure 1. Those 6 weeks are designed to assess whether any potential effects are persisting after acute treatment.

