### Measurements

2.5.

At the inclusion visit (week −3 to 0), after giving informed consent, the following baseline characteristics will be recorded during a pre-screening: Age (years), gender (male/female), ethnicity (White, black, or others), height (cm), weight (kg), alcohol use in units (one unit defined as 12 g pure alcohol), tobacco use (package years), time since diagnosis of AD (months) and education (years). The participants will further have their medical history reviewed including current medication, physical examination, and blood samples (plasma-Alat, plasma-HbA1C, plasma-Sodium, plasma-Potassium, and plasma-Creatinine), this is done to rule out any undiagnosed diseases and establish baseline values in case of adverse events. To assess the effects of the treatment, the following examination battery will be administered at baseline (week 0), post-intervention follow-up (week 26), and no-intervention follow-up (week 32): EEG steady state visual evoked potential (SSVEP) during exposure to the allocated device (not at week 32), resting-state electroencephalography (rs-EEG) (Cassani et al., 2018), Alzheimer’s Disease Assessment Scale-Cognitive Subscale Plus Executive Function & Functional Ability (ADAS-Cog Plus EF&FA) (Skinner et al., 2012), Alzheimer’s Disease Cooperative Study – Activities of Daily Living (ADCS-ADL) (Galasko et al., 1997), Montreal Cognitive Assessment (MoCA) (Nasreddine et al., 2005), Magnetic resonance (MR) imaging (high-resolution T1-weighted imaging, functional Blood Oxygen Level Dependent imaging (BOLD-fMRI), perfusion-weighted MR imaging and MR spectroscopy) and blood-based biomarkers (plasma Aβ42/40-ratio, plasma tau181, plasma tau231, plasma neurofilament light chain, and plasma glial fibrillary acidic protein). In addition to these time-specific measurements, continuous actigraphy will be collected by a wrist-worn actigraph to assess activity and changes in the circadian rhythm. All data will be recorded by trained personnel. The EEG will be recorded in a designated room, shielded from outside electrical interference using 25 gel-mounted electrodes arranged according to the international 10–20 system with additional electrooculographic (EOG) and electrocardiographic (ECG) electrodes. The cognitive testing will be performed by trained personnel with experience in neuropsychological testing. The MR scan will be performed on a 3T scanner (Siemens Magnetom Vida, Siemens Healthcare). Actigraphy will be recorded using a wrist-worn actigraph (ScanWatch, Withings).

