### Statistical methods

2.9.

The demographics will be reported at exact values for each arm to characterize each arm.

Full completion of all datasets in a clinical trial like this is unlikely; therefore, two different populations will be used for analysis. The first population will be used to assess the effect of the treatment and will be the per protocol population (PPP). The PPP is defined by all data points available for analysis. The other population is the intention to treat (ITT) population. The ITT will be used when assessing safety and feasibility outcomes. This is to ensure that participants who drop-out due to adverse events are being evaluated as part of the study.

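### Last observation carried forward, with no outcome visit between weeks 0 and 26, gives zero change to anyone lost before week 26 and conflicts with the plan's own efficacy set and sample size

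*Protocol article*

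**What the plan says.** All references are to the protocol article.

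- **Section 2.7, Withdrawal and drop-out:** when participants drop out or data are otherwise missing, "a last observation carried forward approach will be used to handle the missing data". No outcome, visit or analysis population is exempted.
- **Section 2.5, Measurements:** "the following examination battery will be administered at baseline (week 0), post-intervention follow-up (week 26), and no-intervention follow-up (week 32"). No battery visit lies between weeks 0 and 26. There are two special cases. The first is "EEG steady state visual evoked potential (SSVEP) during exposure to the allocated device (not at week 32"). The second is that "continuous actigraphy will be collected by a wrist-worn actigraph".
- **Section 2.6, Outcome measures:** the primary outcome concerns change in gamma power from week 0 to week 26. Most secondary outcomes are changes from week 0 to weeks 26 and 32.
- **Section 2.8, Recruitment and sample size:** 50% drop-out is assumed, giving 124 participants (62 per arm). Section 2.2 instead sets a target of 31 included per arm.
- **Section 2.9, Statistical methods:** the treatment effect is assessed in the per protocol population, and "The PPP is defined by all data points available for analysis".
- **Section 2.1, on the six weeks without intervention:** "Those 6 weeks are designed to assess whether any potential effects are persisting after acute treatment".

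**The concern.** With this schedule, carrying the last observation forward to week 26 means carrying baseline forward. A participant lost before week 26 has one battery measurement, taken at week 0, so the imputed change is exactly zero. The plan expects to lose half its sample, so this could apply to as many as half of the week-26 values.

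Three things are at stake.

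1. A real EEG effect is pulled towards zero.
2. In outcomes that worsen over time, such as cognition, function and atrophy, the rule freezes decline in those who leave. If one arm loses more people, that arm looks better with no treatment effect at all.
3. At week 32 the rule fills some off-treatment values with end-of-treatment values, at the visit designed to test persistence.

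The rule also counts imputed values as if they had been observed, whereas the sample size and the definition of the efficacy set suggest that drop-outs contribute nothing.

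**Working it through.** **Inputs.** From section 2.8: means at 6 months of 2.7 and 0 dB, SD 3.2 dB in both groups, power 90%, type 1 error 5% (taken as two-sided), equal allocation, drop-out 50%. Assumed here: equal baseline means in the two arms, drop-out unrelated to outcome and, for change scores, a correlation of 0.5 between baseline and week 26.

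**1. The plan's own figure.** The standardised difference is 2.7/3.2 = 0.844. The exact two-sample t calculation gives 30.5, so 31 per arm, with power 90.5%. Allowing for drop-out, 31/(1 − 0.5) = 62 per arm, 124 in total. The stated figure reproduces, and it treats drop-outs as giving no data.

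**2. Dilution.** With drop-out proportion d in both arms, the expected difference is (1 − d) × 2.7:
- d = 0.2: 2.16 dB
- d = 0.3: 1.89 dB
- d = 0.5: 1.35 dB

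**3. Power at d = 0.5.** The mixture of completers and carried values adds d(1 − d) × 2.7² = 0.25 × 7.29 = 1.82 to the variance in the active arm.

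*Change scores.* With correlation 0.5 the SD of change is 3.2 × √(2 × (1 − 0.5)) = 3.2. Drop-outs sit at exactly zero, so the variances are 0.5 × 10.24 + 1.82 = 6.94 (active) and 0.5 × 10.24 = 5.12 (placebo). The pooled SD is √6.03 = 2.46.

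*Week-26 values.* Carried baselines keep SD 3.2, so the variances are 10.24 + 1.82 = 12.06 and 10.24. The pooled SD is √11.15 = 3.34.

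| Randomised per arm | Carried forward, change scores | Carried forward, week-26 values | Completers only |
|---|---|---|---|
| 62 | about 87% | 61% | 90% (31 per arm) |
| 31 | about 58% | 35% | 62–64% (15.5 to 16 per arm) |

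The change-score figures are simulated; the formula gives 86% and 57%.

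**4. Unequal drop-out, no treatment effect.** If both arms decline by x on average, the false difference is x times the difference in drop-out proportions. At 60% against 40% it is 0.20x, in favour of the arm with more drop-out. Simulated type I error on change scores, for a decline of 0.5 to 1 SD:
- 50/50: about 5%
- 55/45: 6–10%
- 60/40: about 8–15% with 31 per arm and 12–26% with 62 per arm

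The splits and the size of the decline are assumptions; the article gives neither.

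**5. Week 32.** Participants seen at week 26 but missing at week 32 have the end-of-treatment value copied into the off-treatment visit, which builds in persistence. Those lost before week 26 carry baseline, which pulls any apparent persistent effect towards zero. The article gives no timing of drop-out, so the net direction cannot be determined.

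**6. The sections side by side.** Section 2.7 imputes all missing data. Section 2.9 bases efficacy on available data points. If available means observed, 2.9 contradicts 2.7. If it includes carried values, the effects in steps 2 to 5 follow. Section 2.8 fits the first reading.

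**The case against.** The strongest reply is that the rule may never reach the efficacy analysis. Section 2.9 can be read as observed data only, and the doubling in section 2.8 agrees with that. This shows that the plan does not settle the matter, but it does not rescue section 2.7, whose wording has no exception. A statistical analysis plan that follows 2.7 inherits the problem, and one that departs from it contradicts the published protocol.

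Other points narrow the concern, and they stand:

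- **Scope.** A reader might infer that every comparison and every drop-out is affected. Actigraphy is continuous, so its last value need not precede treatment. Adverse-event counts are untouched. Participants lost after week 26 have a real week-26 value.
- **SSVEP.** It is recorded on the allocated device at week 0 as well. If the 40 Hz response is acute, it may already be present then, and carrying it forward would not dilute the week-26 level. Change would still be forced to zero.
- **Power.** A reader might infer a large loss from the 61% and 35% figures alone. The primary outcome is framed as change, and on change scores the loss at 62 per arm is only from about 90% to 87%. The halving of the estimate holds on both scales.
- **False positives.** These need both unequal drop-out and a mean change over time. The article gives a single drop-out rate and describes devices that cannot be told apart, so it gives no particular reason to expect a 20-point gap between arms.
- **Persistence.** A reader might infer that the week-32 result is biased towards persistence. The two groups of drop-outs pull in opposite directions, so this does not follow.

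**Conclusion.** The concern holds for visit-based efficacy outcomes. Section 2.7 fixes a rule that, with this schedule, assigns zero change to anyone lost before week 26, and it is not reconciled with sections 2.8 and 2.9.

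At the plan's own 50% drop-out the expected difference falls from 2.7 to 1.35 dB, given equal baseline means and drop-out unrelated to outcome. The loss of power ranges from slight (change scores, 62 per arm) to severe (week-26 values), depending on an analysis scale that the article does not fix. Inflated type I error in declining outcomes is conditional on unequal drop-out: none at 50/50, and up to about 26% at an assumed 60/40 split with 62 per arm. The documents do not support a claim that a false positive is to be expected, nor any stated direction of bias at week 32.

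Because the rule bears on the primary estimate under the plan's own assumptions and is cheap to replace, it should be changed before unblinding.

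**What to change.** Delete last observation carried forward from section 2.7, and state in 2.7, 2.8 and 2.9 one consistent account of which participants and values enter the efficacy analysis. Then:

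- **Outcomes measured at weeks 26 and 32:** a baseline-adjusted, likelihood-based repeated-measures model of the observed data under missing-at-random.
- **SSVEP:** baseline-adjusted ANCOVA at week 26, since it is not recorded at week 32 and a joint model of the two visits cannot apply.
- **If all randomised participants are to contribute:** put baseline in the response vector (a constrained longitudinal model) or use multiple imputation. With baseline as a covariate only, participants with no post-baseline visit add nothing to the likelihood.
- **Sensitivity:** a delta-adjusted or reference-based analysis, with drop-out reported by arm and reason.

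The cost is wording and modest programming, with no new data. The price is reliance on missing-at-random, which the sensitivity analysis is there to probe.

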### Recruitment and sample size

2.8.

Participants will be recruited through contact with their usual healthcare professionals on the Danish Island of Zealand with a population of approximately 2.7 million inhabitants (Danmarks Statistik, 2021).

The sample size calculation is based on the primary outcome and has been based on effect sizes reported (Xing et al., 2018; Jones et al., 2019). The estimation is carried out using R version 3.6.3 with “pwr” version 1.2–2 with the following assumptions: (1) Two-sample *T*-test assuming equal variance, (2) Equal allocation, (3) Signal-to-noise (SNR) ratio at 40 Hz of 2.7 dB in the active treatment group and 0 dB in the placebo group at 6 months, (4) Standard deviation of 3.2 dB in both groups, (5) A power of 90%, and (6) Type 1 error of 5%. A 50% drop-out rate is assumed based on previous experience, resulting in a sample size of 124 (62 in each arm).

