**Methods:**

62 patients with mild-to-moderate AD will participate in a randomized, double-blinded, placebo-controlled, parallel-group, and single-center trial. The participants will partake in an enrollment period of 1 month, an intervention period of 6 months, and a 1.5-month post-interventional follow-up period. Prior to the baseline measurement (week 0), the patients will be randomized to either active or placebo intervention from baseline (week 0) to post-intervention follow-up (week 26).

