### Participants

2.2.

This study will recruit a minimum of 62 patients with mild to moderate AD. Recruitment will continue until each arm reaches the target of 31 included participants. The participants must be above the age of 55, provide informed consent and match the following in- and exclusion criteria.

Inclusion criteria:

– Diagnosed with probable mild to moderate AD based on the National Institute on Aging and Alzheimer’s Association (NIA-AA) criteria (Jack et al., 2018)– Speak Danish fluently– >8 years of education– Pass a color-blindness test (Ishihara color test)– Have visual and auditory capabilities, and language skills necessary for neuropsychological testing– Participants must have a designated caregiver, who is available to support the participant in complying

Exclusion criteria:

– Visual acuity >0.5– Significant abnormalities related to relevant parts of the brain, e.g., the visual system, prefrontal cortex, or hippocampus, or relevant lesions detected by pre-trial imaging– Prior history of diseases related to the brain or the visual system (excluding AD)– Use of antiepileptic medication, neuromodulatory medication or high doses of sedatives– History of substance abuse within the last 2 years– Any significant systemic illness or unstable medical condition, which could lead to difficulty complying with the protocol (at the discretion of the PI)

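### The abstract and section 2.2 set the trial at 62 patients, but section 2.8 calculates 124; the 90% power holds only if the 31 per arm are evaluable at week 26, which the protocol does not say

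*Protocol article*

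**What the plan says.** The protocol article gives the size of the trial in three places.

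- Abstract, Methods: "62 patients with mild-to-moderate AD will participate in a randomized, double-blinded, placebo-controlled, parallel-group, and single-center trial".
- Section 2.2, Participants: "This study will recruit a minimum of 62 patients with mild to moderate AD". The next sentence gives the stopping point: "Recruitment will continue until each arm reaches the target of 31 included participants".
- Section 2.8, Recruitment and sample size: "A 50% drop-out rate is assumed based on previous experience, resulting in a sample size of 124 (62 in each arm").

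The calculation in section 2.8 assumes "Signal-to-noise (SNR) ratio at 40 Hz of 2.7 dB in the active treatment group and 0 dB in the placebo group at 6 months" and "Standard deviation of 3.2 dB in both groups". The test is a two-sample t-test "assuming equal variance, (2) Equal allocation", with 90% power and a 5% type 1 error.

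Two further sections decide what a drop-out contributes. Section 2.7 handles missing data by last observation carried forward. Section 2.9 assesses treatment effect in a per protocol population, defined by the data points available for analysis.

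**The concern.** Section 2.8 arrives at twice the total given in the abstract and in section 2.2. The figure of 62 appears in both places with different meanings: all patients in the abstract and 2.2, one arm in 2.8. This suggests that the number needed for analysis became the recruitment target, with the drop-out allowance left off. The other possibility is that *included* in section 2.2 was meant as completing the trial.

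A site following section 2.2 literally and a site following section 2.8 would run trials that differ twofold in size. The number randomised decides when recruitment stops and how a null primary result can be read. If the smaller number is the one randomised and the assumed drop-out occurs, the 90% power in section 2.8 does not describe the trial being run.

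**Working it through.** **Inputs** (section 2.8 unless noted)

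- Difference: 2.7 − 0 = 2.7 dB. SD: 3.2 dB in both groups.
- Power 90%, type 1 error 5%. Sidedness is not stated; two-sided is inferred below.
- Drop-out 50%.
- Recruitment target: 31 included per arm (section 2.2).

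**Step 1. Reproduce the plan's figure.** Standardised effect d = 2.7 / 3.2 = 0.844. Per-arm n for a two-sample t-test (noncentral t, as in the pwr package):

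- Two-sided 5%: n = 30.51, rounded up to 31.
- One-sided 5%: n = 24.77, rounded up to 25.

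Inflation for drop-out is n / (1 − drop-out rate). Two-sided: 31 / 0.5 = 62 per arm, and 2 × 62 = 124 in total. This matches section 2.8 exactly. One-sided: 25 / 0.5 = 50 per arm, which does not match. The calculation was therefore two-sided, and its arithmetic is correct. Section 2.8 does not print 31 per arm, but that is the number its inputs require before inflation, and 2 × 31 = 62 is the total in the abstract.

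**Step 2. Power if 31 per arm are evaluable at week 26.** With d = 0.844 and n = 31, power is 90.5%. At 50% drop-out this needs 124 randomised.

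**Step 3. Power if 31 per arm are randomised and drop-outs are excluded.** Evaluable n = 31 × (1 − drop-out rate).

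| Drop-out | Evaluable per arm | Power |
|---|---|---|
| 50% (the plan's figure) | 15.5 | 62% (61% at 15, 64% at 16) |
| 30% (illustration) | 21.7 | 77% |
| 20% (illustration) | 24.8 | 83% |

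The difference detectable with 90% power is 3.92 dB at 15 per arm and 3.79 dB at 16, against 2.7 dB in the plan. If drop-out varies at random around 50% in each arm, average power is about 61%.

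**Step 4. Power if 31 per arm are randomised and drop-outs are kept by last observation carried forward.** The analysed n stays at 31 per arm, but the carried values dilute the effect. As an illustration, suppose half of each arm carries its baseline value forward, so that the mean difference halves to 1.35 dB, and the SD stays at 3.2 dB. Then d = 1.35 / 3.2 = 0.422 and power is about 37%. The halved effect and unchanged SD are assumptions of this illustration and are not stated in the protocol.

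**The case against.** The strongest reply is that section 2.2 sets a minimum and lets recruitment continue until the target is met. Read that way, the 31 per arm are evaluable patients, up to 124 are recruited, sections 2.2 and 2.8 agree, and power is about 90%. This reading cannot be excluded, so it would be too strong to say that the two sections can never both be followed. The text gives it little support, however. Section 2.2 says *included*; section 2.5 places the inclusion visit at week −3 to 0, before treatment; the abstract gives 62 as those taking part; and nothing says that drop-outs are replaced. Even on this reading the abstract remains wrong.

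A second reply is that carrying the last observation forward keeps all 31 per arm in the analysis. This stands as far as the count goes: the fall to 15 or 16 per arm follows only if drop-outs are excluded, which section 2.9 suggests and section 2.7 does not. It does not rescue the power, as Step 4 shows.

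A third is that drop-out may be lower than 50%. That is possible, but 50% is the plan's own assumption, said to rest on experience, and power stays below 90% at 20% and 30% as well.

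A reader might infer that the trial simply has 62% power. The documents do not establish that. The figure requires that *included* means randomised, that recruitment ends at the stated minimum, that half drop out, and that drop-outs are excluded.

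**Conclusion.** The point holds as an internal contradiction that must be fixed. The abstract and section 2.2 give 62 patients, section 2.8 gives 124, and no text connects them. The calculation in section 2.8 is sound in itself; 62 in total is its result before the drop-out allowance.

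The loss of power is conditional:

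- If 31 per arm complete week 26, power is about 90%, and the error is an abstract that understates the number randomised by half.
- If 31 per arm are randomised, half drop out and drop-outs are excluded, power is about 62% (61% to 64%).
- If 31 per arm are randomised and drop-outs are carried forward, power depends on how far the effect is diluted; the illustrative case gives about 37%.

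All of these rest on the stated 2.7 dB and 3.2 dB and on a two-sided 5% test, which is inferred because it alone reproduces the plan's number. The discrepancy in the number of patients is certain; which power applies is not.

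**What to change.** State one number randomised in the abstract, section 2.2 and section 2.8. In section 2.2, replace *included* with either *randomised* or *completing week 26*.

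- If 124 are randomised, correct the abstract and section 2.2.
- If 62 are randomised, remove the 124 (62 per arm) from section 2.8 and restate the power for the assumed drop-out and the analysis actually used. With drop-outs excluded this is about 62% at 50% drop-out; about 77% at 30% and 83% at 20% can be added as illustrations. If last observation carried forward is the analysis, 62% should not be inserted. Compute the power for that analysis, with the assumed dilution stated.

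In either case, say in section 2.8 that the test is two-sided.

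The cost is wording only. The downside is that, if 62 are randomised, the stated power becomes less favourable.
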